### 1.3. INTERVENTION (I)

The BETER guidelines provide personalised risk-based screening recommendations according to the risk of late adverse treatment effects associated with a survivor's sex, current age, age at lymphoma diagnosis and lymphoma treatment (1.3.1.). The intervention in the proposed study consists of BETER survivorship care, i.e. personalised risk-based screening for and treatment of CVD (including risk factors for CVD), breast cancer and hypothyroidism, and infection prevention measures (incl. vaccination) in case of functional asplenia. BETER survivorship care also includes lifestyle recommendations (see 1.3.1.) and is administered in clinical practice at an outpatient clinic in a BETER participating centre (further denoted as BETER clinic).

#### 1.3.1. BETER Screening Recommendations for Late Adverse Effects after Lymphoma Treatment

##### 1.3.1.1. Cardiovascular Disease

RISK: standardized incidence ratio (SIR) of 2-6 and a 40-year cumulative incidence of 50% (at age 65) (16).

SUBGROUP OF LYMPHOMA SURVIVORS: treated with cardiotoxic chemotherapy (doxorubicin, epirubicin, rubidomycin, daunorubicin, mitoxantrone) with cumulative doses equivalent to doxorubicin =300 mg/m^2, radiotherapy to the mediastinum or radiotherapy to the mediastinum in combination with cardiotoxic chemotherapy, independent of cumulative dose.

SCREENING: screening of cardiovascular risk factors every 5 years, up to age 70 (medical history, physical examination and blood tests: lipid spectrum, glucose, biomarkers BNP or NTproBNP as a reference for follow-up), screening for valvular disease and subclinical heart failure by cardiac ultrasound only once 15 years after diagnosis in case of radiotherapy mediastinum and every 5 years in case of cardiotoxic chemotherapy (with/without mediastinal radiotherapy) and ECG (once as a reference).

TREATMENT AND/OR PREVENTION OF LATE ADVERSE EFFECTS: treatment of cardiovascular risk factors hypertension and hypercholesterolemia, treatment in case of subclinical decrease of ejection fraction and lifestyle recommendations in accordance with general population guidelines.

##### 1.3.1.2. Breast Cancer

RISK: SIR 4-6 and a 30-year cumulative incidence of 17-26% at age 55 (15).

SUBGROUP OF LYMPHOMA SURVIVORS: women treated with radiotherapy on chest and/or axillae before the age of 40 years.

SCREENING: age 25-30: annual clinical breast examination and magnetic resonance imaging (MRI); age 30-60: annual clinical breast examination, mammography and MRI; age 60-70: biennial clinical breast examination and mammography; age 70-75: biennial mammography through population screening.

TREATMENT AND/OR PREVENTION OF LATE ADVERSE EFFECTS: take previous chest radiation treatment into account and consider risk of cardiomyopathy when using anthracyclines.

##### 1.3.1.3 Thyroid Dysfunction

RISK: absolute risk of 44-67% 25 years after treatment (3).

SUBGROUP OF LYMPHOMA SURVIVORS: treated with radiotherapy to the thyroid region.

SCREENING: every 1-3 years palpation of the thyroid gland and annual laboratory examination of thyroid-stimulating hormone; if abnormal free tetra-iodothyronine (FT4).

TREATMENT AND/OR PREVENTION OF LATE ADVERSE EFFECTS: in accordance with general population.

##### 1.3.1.4 Overwhelming Post-Splenectomy Infections

RISK: relative risk up to 20 (17).

SUBGROUP OF LYMPHOMA SURVIVORS: treated with splenectomy, splenic radiotherapy (mean dose >20 Gy) or stem cell transplant.

SCREENING: none.

TREATMENT AND/OR PREVENTION OF LATE ADVERSE EFFECTS: vaccinations for Pneumococcus (start with Prevenar-13, followed by Pneumovax-23 two months later; Pneumovax-23 every 5 years), Haemophilus Influenzae B once, Meningococcus once, Influenza annual; medical alert card, travel advice and antibiotics on demand.

### 1.4 COMPARATOR (C)

Absence of structured survivorship care after discontinuation of follow-up for lymphoma recurrence (patients were usually

discharged 5 years after lymphoma treatment).

### 1.5 FOLLOW-TIME (T)

To facilitate follow-up of at least 5 years at the BETER clinics, the follow-up of lymphoma survivors in the intervention group starts in 2013-2016, when they were first invited to attend the BETER clinic, and ends in 2021-2024 at their most recent BETER visit. The start of follow-up of survivors in the control group will correspond to that of the intervention group and ends at their first BETER visit in 2021-2024. The follow-up of survivors who do not attend the BETER clinic (i.e. non-attenders in both the intervention and control groups) ends on completion of the mailed questionnaires. Furthermore, if survivors either in the intervention group or comparison group die during follow-up, follow-up ends at death. Expected median follow-up time is 8 years.

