#### 1.2. PATIENT (P)

##### 1.2.1. Patient population

The study will be nested in a large nationwide retrospective cohort study of HL survivors treated in 27 Dutch centres between 1965 and 2012 (15,16). This cohort was originally established in the 1980s-1990s to examine the late effects of HL treatment; since then the cohort has been periodically extended with more treatment centres, patients diagnosed in more recent years and with diffuse large B-cell lymphoma (DLBCL) survivors diagnosed between 1989 and 2012. Lymphoma survivors eligible for BETER survivorship care were successfully treated at least 5 years ago for HL or DLBCL at age 15-60 years and are less than 70 years of age at invitation. The patient population in this evaluation study will only consist of HL survivors eligible for BETER survivorship care, as they were the first to be invited to the BETER clinics in 2013-2016 due to their higher risk of late adverse treatment effects compared to DLBCL survivors.

1.2.2. Intervention group: the first 450 HL survivors between 2013 and 2016 who were invited for screening for late adverse treatment effects in the BETER centre where they were originally treated for HL. With attendance rates ranging between 60-70%, around 300 HL survivors in the intervention group are expected to receive screening at the BETER clinics.

1.2.3. Control group: frequency matched group of 450 HL survivors, eligible for BETER screening for late adverse treatment effects in 2013-2016, but not yet invited because the centre where they were originally treated for HL does not start a BETER clinic until 2021-2024. So, the control group will be invited in 2021-2024.

Controls will be matched with the intervention population on the following criteria:

- sex
- age at diagnosis ( $\pm 3$  years)
- year of diagnosis ( $\pm 3$  years)
- lymphoma treatment characteristics associated with increased risk of CVD, breast cancer, hypothyroidism and functional asplenia (see also 1.3.1.). In practice this implies matching on chest radiotherapy (y/n), neck radiotherapy (y/n), spleen radiotherapy (y/n), splenectomy (y/n) and anthracyclines (y/n + doxorubicin  $\approx 300$  mg/m^2 y/n).

Survivors selected as controls should be alive at the time the corresponding survivor in the intervention group was invited to

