come to the BETER clinic. Of note, matched controls eligible for BETER screening in 2013-2016 who died during follow-up, prior to invitation for BETER screening in a BETER clinic 2021-2024, are eligible for our study.

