#### 1.8.2. Patient level analysis

To assess the impact of BETER survivorship care on screened/treated individuals, outcome parameters will be compared between the first 270 survivors who attended a BETER clinic that started in 2013-2014 and matched survivors who are not (yet) screened and were treated for lymphoma at BETER centres that start a clinic in 2021-2024.

On both levels of analysis, multiple linear regression analysis will be used for continuous outcomes (such as DALYs and health care costs) and Poisson or negative binomial regression analysis will be used for count variables (i.e. yield of previously undiagnosed adverse events). The regression analyses will also take the amount of follow-up time into account, thereby correcting for a possible difference in follow-up time in the intervention and control group.

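### In the patient-level analysis follow-up starts at invitation but exposure is defined by a later visit, so deaths in between can count only among the controls

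*Protocol*

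**What the plan says.** Section 1.5 sets one start of follow-up for the whole intervention group: it "starts in 2013-2016, when they were first invited to attend the BETER clinic". On the controls it adds: "The start of follow-up of survivors in the control group will correspond to that of the intervention group". No other start is given for the patient-level analysis.

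Section 1.8.2 defines the exposed group of that analysis as "the first 270 survivors who attended a BETER clinic that started in 2013-2014". The comparators are "matched survivors who are not (yet) screened".

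The survival condition for controls is in 1.2.3: "Survivors selected as controls should be alive at the time the corresponding survivor in the intervention group was invited". The same section says that matched controls "who died during follow-up, prior to invitation for BETER screening in a BETER clinic 2021-2024, are eligible for our study". Section 8.5.1 repeats both rules.

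Under 1.6.1.2, each death adds the standard life expectancy at the age of death to the DALYs. The only time-related adjustment in 1.8.2 is for length of follow-up. Section 1.8.1 accepts that an unbiased analysis should not select on attendance, and it ranks intention to screen as the most valid approach.

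**The concern.** Three rules that the protocol itself fixes do not fit together in this one analysis: time zero is the invitation, exposure needs a later event (a visit), and controls need to be alive only at the invitation. The time between invitation and first visit is therefore immortal for attenders and not for controls.

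Deaths carry full YLL, so a few deaths counted on one side only can move a mean DALY difference. The patient-level effect is not a side figure either: the 0.62 DALY gain is the health effect reported in the efficiency appendix. Adjusting for total follow-up time does not help, because the attenders' follow-up time includes the protected interval.

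**Working it through.** **The plan's own figures.** Section 1.7.3 gives 274 per arm and a detectable difference of 0.24 SD. Both reproduce: 0.65 × 452 / 1.07 = 274.6, and (1.960 + 0.842) × √(2/274) = 0.239. The expected patient-level effect (1.7.1) is 1.18 − 0.56 = 0.62 DALY over 5 years. None of this is disputed.

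**Who can contribute a death between invitation and first visit**

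| | Invited survivor, later visit needed | Matched control |
|---|---|---|
| Start of follow-up (1.5) | invitation | same date |
| Must be alive at (1.2.3, 1.8.2) | first visit | invitation |
| Dies in the interval | not an attender, so not in the analysis | kept, full YLL |

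**Size of the bias if BETER has no effect.** The bias is *r* × *f* × *g*, where
- *r* is the control DALY rate, 1.18 / 5 = 0.236 per year (1.7.1), taken as constant;
- *f* is the YLL share of DALYs, not given and assumed to be 0.7-0.9;
- *g* is the gap from invitation to first visit in years, not given.

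The bias arises once, but the effect may keep accruing. The last column therefore sets it against an 8-year effect (the expected median follow-up in 1.5), assuming linear accrual: 0.62 × 8/5 = 0.99.

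| Gap | 0.236 × (0.7-0.9) × *g* | Share of 0.62 | Share of 0.99 |
|---|---|---|---|
| 1 month | 0.014-0.018 | 2-3% | 1-2% |
| 3 months | 0.041-0.053 | 7-9% | 4-5% |
| 6 months | 0.083-0.106 | 13-17% | 8-11% |
| 12 months | 0.165-0.212 | 27-34% | 17-21% |

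**Check by simulation.** Assumptions: no effect, exponential death times, 8 years of follow-up and 30 years lost per death. With a 3-month gap and a YLL share of 50%, mean YLL is 0.929 in all survivors and 0.900 in those alive at the end of the gap, a difference of 0.029 (formula 0.0295). With 12 months and 100%, the means are 1.821 and 1.601, a difference of 0.220 (formula 0.236). Over this range about 0.3 to 2 deaths per 270 people fall in the gap.

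**The sentence in 1.7.3 that points elsewhere.** It counts 274 survivors in each arm at 65% attendance. It justifies 7% incomplete data by saying that these survivors attend, or have attended, a clinic. Read literally, controls would also have to survive until a visit in 2021-2024. The YLL removed from the control arm over about 8 years would then be 0.236 × (0.7-0.9) × 8 = 1.32-1.70 DALY, far more than the term above and against BETER. Sections 1.2.3 and 1.8.2 say the opposite: deceased controls stay eligible, and controls are not yet screened.

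**The case against.** The best defence is that this is the supporting analysis. Section 1.8.1 already ranks it below intention to screen and concedes the problem of selecting on attendance. That stands and limits the weight of the point. It does not answer it, because immortal time is a separate fault with its own remedy.

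The second objection concerns size. A reader might infer from the 12-month row that up to a third of the expected benefit is an artefact. The document does not support that: it gives no gap, and with one month the bias is 2-3% of 0.62. A reader might also infer that years of life lost dominate the DALYs, but 1.7.1 splits them by disease and never by YLL and YLD. In addition, 1.8.2 takes the first 270 attenders while 1.2.2 expects around 300, so the latest attenders may drop out. These objections stand.

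The third concerns direction. Under the literal reading of 1.7.3 the net bias could run against BETER. That reading conflicts with 1.2.3 and 1.8.2, so it does not overturn the point, but the conflict must be resolved.

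Finally, a landmark or delayed-entry rule is often left to the statistical analysis plan. Here, however, the protocol has itself fixed a start date for the whole intervention group, and that date is wrong for this analysis.

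**Conclusion.** The misalignment is real and follows from the protocol's own rules. As written, deaths between invitation and first visit can count only among controls in the patient-level analysis, which favours BETER in the fatal part of the DALYs. Non-fatal events before the visit can still be counted in attenders.

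The size is open: about 0.014-0.018 DALY at 1 month, 0.04-0.05 at 3, 0.08-0.11 at 6 and 0.17-0.21 at 12. These figures rest on a constant rate of 0.236 per year and an assumed YLL share of 70-90%. They should be read against 0.62 DALY over 5 years, and form a smaller share if the effect keeps accruing over 8 years. The direction assumes that controls are not selected on later attendance.

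A reader might carry the point over to the main result. The documents do not support that: intention to screen counts everyone invited from the date of invitation, so it has no protected interval. The correction is worth making because it is cheap.

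**What to change.** In 1.5 and 1.8.2, for the patient-level analysis only: start each attender's follow-up at the first BETER visit, require the matched control to be alive on that date, and start the control's follow-up there. Keep invitation as the start for intention to screen.

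In the same edit, reconcile 1.7.3 with 1.2.3 and 1.8.2 by stating that controls in the patient-level analysis are not selected on later attendance, and revise the reason given for 7% incomplete data to match.

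No new data are needed. Data from all BETER visits are already collected (1.6.1.1), and dates of death are known for both groups (8.5.1). The costs are slightly shorter follow-up, a second survival check with replacement of some controls, and a time zero that differs from the intention-to-screen analysis, so the two estimates no longer cover quite the same period.

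The change does not remove selection by attendance. Section 1.6.2.2 reports that adverse events already diagnosed elsewhere and unwillingness to attend were the commonest reasons for staying away. The patient-level analysis should therefore remain supportive.

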**SAMPLE SIZE CALCULATION/DATA ANALYSIS**

Regression analyses will be performed at intention to screen and patient level. At intention to screen level, expecting 5-year accumulation of 0.78 DALYs in the intervention vs. 1.18 in the control group, with  $\alpha=0.05$  and 80% power to detect a difference of 0.20 standard deviation and larger, we need 452 patients in each study arm. This also allows for detection of medium effect sizes in sub analyses.

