For the intervention group trained data managers will access the BETER medical records in the BETER clinics and collect the relevant data from all BETER visits, including all screening/diagnostic tests during follow-up and their results. For all survivors included in the study (intervention and comparison groups) we will obtain information on the incidence of clinical events of interest through linkage with disease registries. Information on second malignancies will be obtained from The Netherlands Cancer Registry, information on cardiac interventions will be obtained from The National Heart Registry, information on hospital admissions for CVD and serious infections (overwhelming post-splenectomy infections) will be obtained from Dutch Hospital Data and cause of death for those who died during follow-up will be obtained from Statistics Netherlands. We will also approach the general practitioners of all patients to obtain data on CVDs (especially those not requiring hospital admission, such as angina pectoris), cardiovascular risk factors (hypertension and hypercholesterolemia) and hypothyroidism.

Survivors' informed consent for the above data collection is asked at the first visit to a BETER clinic. For included survivors who choose not to visit a BETER clinic informed consent for linkage with disease registries and approach of general practitioner is requested by mail. Currently over 97% of all patients visiting a BETER clinic has provided consent. Informed consent for the control group will be obtained during the patients' first visit at a BETER clinic in 2021-2024 and is not necessary for deceased individuals.

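### Follow-up starts together but ends at visit- and questionnaire-driven events that differ by arm, so deaths and late events fall in non-comparable windows

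*Protocol*

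**What the plan says.** Section 1.5 gives both groups the same kind of start: "The start of follow-up of survivors in the control group will correspond to that of the intervention group". The end depends on group and behaviour. For the intervention group, follow-up "ends in 2021-2024 at their most recent BETER visit". For controls it "ends at their first BETER visit in 2021-2024". For non-attenders in both groups it "ends on completion of the mailed questionnaires". Then: "if survivors either in the intervention group or comparison group die during follow-up, follow-up ends at death". The section adds: "Expected median follow-up time is 8 years".

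Other sections bear on this:

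- Section 1.2.3 keeps matched controls who died before their centre invited them.
- Section 1.6.1.1 covers survivors in both groups: "we will obtain information on the incidence of clinical events of interest through linkage with disease registries".
- Section 1.8.2 says the regressions will account for the amount of follow-up time.
- Section 8.5.1 says date and cause of death are known for invited survivors whether or not they attended.

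**The concern.** A comparison of accumulated burden needs the same observation window in both groups. Here the window closes on events that require a person to be alive and to come to a clinic or return a form, and the closing event is not the same in the two groups. Among attenders it is the last of a series of visits on one side and the first visit ever on the other.

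The primary burden measure is years of life lost plus years lived with disability. If deaths or late events fall inside the window in one group and outside it in the other, a DALY and cost difference can appear that has nothing to do with BETER care. Section 1.8.1 presents the comparison as one that mimics randomization, which presupposes a common window.

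**Working it through.** **1. The plan's own figures.** Intention-to-screen mean in the intervention group: 0.65 × 0.56 + 0.35 × 1.18 = 0.777 DALY. Difference from 1.18: 0.403, stated as 0.40. Sample size for 0.20 SD, two-sided 0.05, 80% power: 2 × (1.960 + 0.842)² / 0.20² = 392.4, so 393 per arm; 393 × 1.15 = 452. Both stated figures reproduce, and neither depends on the end rule.

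**2. End rules side by side (section 1.5).**

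| Survivor | Intervention | Control |
|---|---|---|
| Attends | most recent visit, 2021-2024 | first visit, 2021-2024 |
| Does not attend | questionnaire completed | questionnaire completed |
| Dies during follow-up | death | death |
| Alive, returns no questionnaire | not defined | not defined |
| Attended, but no visit in 2021-2024 | not defined | does not arise |

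The last row is not remote. Section 1.3.1.1 sets cardiovascular risk-factor screening every 5 years. A survivor first seen in 2014 and followed strictly at that interval is seen in 2019 and 2024, with nothing in 2021-2023.

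**3. Where a death falls.** The death rule covers deaths during follow-up, so it depends on the end date it is meant to supplement. Two readings are open for intervention attenders:

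- *Literal.* Follow-up closes at the most recent visit. Every death comes after the last visit, so no attender's death counts. Control deaths before first invitation do count. This favours the intervention.
- *Deaths to the data cut count, but living attenders stop at their last visit.* Deaths between last visit and cut enter the numerator, while the survivors' person-time over the same period does not. This works against the intervention.

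**4. Illustration of the second reading with no treatment effect.** Assumptions, none from the protocol: equal death hazard in both groups, 1% or 2% per year; entry uniform over 2013-2016; data cut mid-2022 or mid-2024; control first visit uniform from 2021 to the cut; attenders only; 1,000,000 simulated per group.

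| Visit interval | Death rate ratio, attenders vs controls (true value 1.00) |
|---|---|
| 1 year | 1.05-1.08 |
| 2 years | 1.11-1.14 |
| 5 years | 1.33-1.47 |

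These ratios already use person-time as the denominator. The ratio of cumulative death proportions is 1.10-1.22. The five-yearly row extends the last-visit rule to people whose last visit precedes 2021, a case section 1.5 does not cover. Mean follow-up ranges from 1.6 years shorter in the intervention group (4.91 vs 6.52) to 1.2 years longer (8.60 vs 7.44), so even the direction of the length difference is open.

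**5. Weight of one death.** Section 1.6.1.2 values a death at standard life expectancy. Assuming 25-30 years at about age 52, one death counted or missed among 450 moves an arm mean by 25/450 = 0.056 to 30/450 = 0.067 DALY, or 14-17% of 0.40.

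**6. What the follow-up-time adjustment can do.** At 1.18/5 = 0.236 DALY per year, a 1-year difference in mean follow-up gives a crude gap of 0.24 DALY, 59% of 0.40. Adjustment addresses that. It cannot bring back deaths outside the window, remove the distortion in step 4, or supply missing end dates. Follow-up time is also shortened by death, which is part of the outcome, and years of life lost arrive as a lump sum rather than accruing with time.

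**The case against.** The strongest reply is that the plan foresees unequal follow-up and adjusts for it, and that ascertainment is even-handed: registries, GPs and hospital records are used for everyone (sections 1.6.1 and 1.6.1.1), and deaths are known in both groups (section 8.5.1). That stands as far as it goes. The sources are the same; the problem is which of the known events lie inside follow-up. Section 8.5.1 makes the literal reading less likely but does not say where the window closes. The questionnaire rule is the same in both groups, so the arm contrast is last versus first visit among attenders. It is also fair that closing controls at their first visit keeps them unexposed to BETER care, and any replacement must preserve that.

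Four stronger readings are tempting and not supported:

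- *A fixed loss in the intervention arm.* A reader might multiply 65% attendance, the screened rate 0.56/5 = 0.112 per year and an assumed gap of 0.5-2.5 years to get 0.04-0.18 DALY, or 9-45% of 0.40. This counts lost DALYs without the lost person-time, and divides a loss late in a roughly 8-year window by a 5-year difference. It also ignores that control attenders are cut at a visit too: by the same method a 1-year control gap loses 0.65 × 0.236 = 0.153 DALY, against 0.65 × 0.112 = 0.073 in the intervention arm.
- *A contradiction with a 5-year outcome.* The summary's wording, "expecting 5-year accumulation of 0.78 DALYs in the intervention vs. 1.18 in the control group", is a sample-size expectation. Section 1.7.1 says actual follow-up should be longer, and the 5-year horizon in section 2.1 belongs to the cost-effectiveness analysis.
- *Uniformly long visit gaps.* Breast and thyroid checks are annual for the relevant groups (sections 1.3.1.2 and 1.3.1.3), and the practice-variation section reports that some clinics see survivors more often than required. The 1.33-1.47 range is therefore an upper case.
- *An end explicitly tied to health.* This is inferred from section 1.6.2.2, where an adverse event already diagnosed elsewhere is a common reason not to attend, and from the risk-based schedules. It is not stated.

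**Conclusion.** The point holds as a defect in how the window is defined. Starts are aligned; ends are not, and they hang on visits and forms that require survival and attendance. Section 1.5 leaves open how intervention attenders' deaths after their last visit are treated, and the two readings bias the comparison in opposite directions. Direction and size therefore cannot be determined from the document. The no-effect rate ratios of 1.05 to 1.47 show that the distortion can matter even with person-time accounted for, but they rest on assumed hazards, visit intervals and data cuts. The time adjustment in section 1.8.2 is a partial remedy. The two groups of survivors without an end date are a further gap; a statistical analysis plan could fill it, but the stated arm-specific rules would remain.

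**What to change.** Amend section 1.5 for DALYs, mortality, registry and GP events, and health care costs:

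- **Primary:** in both groups, end at death or 5 years from the (matched) index date, whichever is first, regardless of visits or questionnaires. This is the horizon used for the sample size and the cost-effectiveness analysis.
- **Secondary:** a longer common end no later than the opening of the control centre's BETER clinic, applied equally to the matched intervention survivors. A single linkage date after those clinics open in 2021-2024 would count BETER screening and its costs in controls.
- **Visit and questionnaire dates:** use them only to date HRQoL, iPCQ and other questionnaire measures.

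Two details need a sentence each. For 2016 index dates the 5-year point falls in 2021, so say what happens if a control clinic opens earlier that year. The secondary end needs a rule linking controls to intervention survivors, since section 1.2.3 describes frequency matching and section 1.8.1 individual matching.

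The cost is small. Linkages and death data are already planned for everyone, and 393 and 452 per arm are unchanged. Events after 5 years leave the primary analysis, and some GP and hospital records must be read to the common date rather than to the last visit.
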